### Protocol implementation

The SRIIPSS will employ approaches similar to those that have been used in previous sports injury research [9, 23, 30, 33, 52]. It is, however, hypothesized that sports-related injuries and illnesses among Paralympic athletes differ from sport for able-bodied athletes [13, 15]. Existing research has shown that the accessibility, compatibility, interface and design of questions influence the outcome of athletes’ self-report measures [38]. Therefore, we will specifically adapt the protocol to Paralympic sport and thereafter implement the data collection.

For the data recording a commercial product for collection of survey data online (Briteback AB, Norrköping, Sweden; www.briteback.com) will be used. The research team participates in the development of the system to specifically adapt it to, for example, visually impaired athletes. The product enables definition of personal usernames and passwords to protect data from unauthorised use.

A pilot study is planned where we will enroll approximately twenty athletes with different impairments through a convenience sample from the Swedish Paralympic Program. The pilot study aims to evaluate the feasibility of the data collection system, to assure that it works for athletes with physical, visual and intellectual impairments, and to recognize and solve potential problems. The athletes will be asked to fill in the survey during 4 weeks. The pilot study period will end with a cognitive walkthrough to review the primary protocol and also validate the data. This is an evaluation method that aims to assess usability problems of a new tool early in the design process [53]. The athletes and researchers will be asked to evaluate and provide solutions for the proposed system.

Data will be collected from the end of 2016 and continue for approximately 1 year. At the start of the study the athletes fill in baseline information and a psychological profile. The athletes will thereafter be asked to report sports-related injuries and illnesses weekly. The primary outcome of the study is the incidence of injuries and illnesses, divided into a sports-related injury or illness. All data will be based on sport exposure and analyzed for the mechanism of sports-related injuries and illnesses. A closure form will be used when the athlete is back in full training following an injury or illness (Table 2).

**Table 2 Tab2:** Overview of the outcome measures of the SRIIPSS

Outcome measure	Parameter	Measurement

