### Definitions of injury and illness

The main injury definition in the SRIIPSS follows, with some alterations, the definitions previously used for soccer, rugby union, the Olympic Games and athletics [27, 29, 30, 52]:*Any new musculoskeletal pain, feeling or injury that result from participation in Paralympic sport (training or competition) and cause changes in normal training/competition to the mode, duration, intensity or frequency, regardless of whether or not time is lost from training or competition.*

An illness including psychological complaints will be defined as:*Any new illness or psychological complaint that cause changes in normal training/competition to the mode, duration, intensity or frequency, regardless of whether or not time is lost from training or competition.*

The reported incidents will be categorized as ‘sudden onset’ or ‘gradual onset’. A sudden onset incident refers to an incident caused by a specific identifiable episode resulting in a rapid onset of experienced distress. Subsequently, sudden onset injuries will be categorized according to the cause of the incident as: i) traumatic injuries – a condition caused by an identifiable single external transfer of energy (for example, a bone fracture caused by a fall or a ligament tear caused by contact with an obstacle), or ii) overuse injuries – a condition to which no identifiable single external transfer of energy can be associated (examples of overuse sudden onset injuries include tendon tears).

A gradual onset incident refers to a condition that manifests itself over a period of time, or when there is a gradual increase in the intensity of experienced distress, without a single identifiable event being responsible for the condition. Examples of gradual onset conditions include overtraining syndromes and overuse injuries, such as tendinosis and tendinopathies [52].

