### Injury closure form

When the athletes report that they are back in normal training following an injury, they will be asked to fill in an injury closure form with: i) time off full training; ii) final diagnosis; iii) person who made the diagnosis; iv) treatment(s) received; and v) perceived risk factors of injury including impairment related factors. Additionally, there will be the possibility to provide personal comments about the incident reported. The assessment of severity starts on the following day, if the athlete is unable to take part in full and/or normal training and/or competition. Severity will be reported as days absent from training: minor (1–3 days); mild (4–7 days); moderately serious (8–28 days); serious (>28 days-3 months); long-term (3–6 months); and catastrophic injuries [9].

Finally, to describe the patterns of injury, a matrix adjusted to Paralympic sport will be used to categorize the coded injury data according to injury type (nature of injury) and anatomic location (body region). This is based on the Barell Injury Diagnosis Matrix [66] and modified for overuse injuries by Hauret et al. [39] and Jacobsson et el. [31]. The incidents will be classified by mode of onset and will be further analyzed by athlete classification and specific impairment type. A group consisting of two physiotherapists and two physicians with a background in sports medicine and Paralympic sport will classify each self-reported diagnosis of sports-related injuries and illnesses into a diagnostic code according to The International Classification of Diseases (ICD). To confirm the diagnosis of fracture/stress fracture, an x-ray will be required.

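### Injury severity is graded on two conflicting measures with incomplete classes, and injuries still open at study end or drop-out get no severity value

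*Protocol article*

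**What the plan says.** All places are in the protocol article.

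- **Events that need a grade.** Definitions of injury and illness counts any new complaint from sport that changes normal training or competition, "regardless of whether or not time is lost from training or competition". The same section defends this as a way to capture partial time-loss injuries.
- **The scale.** Injury closure form: "Severity will be reported as days absent from training", with minor at 1–3 days, mild at 4–7 and moderately serious at 8–28, then "serious (>28 days-3 months); long-term (3–6 months); and catastrophic injuries [9"]. The last class carries no duration or criterion in the article, only a reference.
- **The item collected.** Same section: "they will be asked to fill in an injury closure form with: i) time off full training".
- **Start of the count.** Same section: "The assessment of severity starts on the following day, if the athlete is unable to take part in full and/or normal training".
- **When the form is filled in.** Injury closure form: "When the athletes report that they are back in normal training following an injury, they will be asked to fill in" it. Protocol implementation: "A closure form will be used when the athlete is back in full training following an injury or illness".
- **Where severity sits.** Table 2 lists severity of injury under the closure form and under no other form.
- **Follow-up.** About 1 year (Protocol implementation). The Discussion names drop-out as a challenge.

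**The concern.** The scale grades absence, while the definition, the form item and the start of the count all refer to departure from full or normal training. An athlete who trains at reduced intensity for weeks is a case by definition and is off full training, yet has no day of absence. Two people coding the same record could grade it differently or leave it ungraded.

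The form is also completed only on recovery. The injuries most likely to lack a severity value are the longest ones, so the missing values depend on the quantity being described.

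At stake is the descriptive severity distribution. The Background (Sports injury research) criticises earlier studies for mainly recording trauma, medical attention or time loss and for not examining severity, so this is a result that the study is meant to improve.

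**Working it through.** The article states no figure for severity, so there is none to reproduce. The check has three steps.

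**1. Are the classes exhaustive and exclusive?** Day counts were run through the stated limits, taking 3 months as 91 days and 6 months as 182 days.

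| Days | Class under the stated limits |
|---|---|
| 0 | none |
| 1, 3 | minor |
| 4, 7 | mild |
| 8, 28 | moderately serious |
| 29 | serious |
| 91 | serious and long-term |
| 182 | long-term |
| 183, 270 | no class with a stated duration |

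There is no class at 0, an overlap at 3 months, and above 6 months only a class without a criterion.

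**2. Do the two measures agree?** Take an injury with 40 days of modified training and no day of absence.

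- Time off full training = 40 days, which is more than 28 days and under 3 months: serious.
- Days absent = 0: no class.

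The 0-day gap is widest if absence is the measure. It does not vanish under the other, because the count starts the day after onset and an injury that affects only the day of onset scores 0.

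**3. How does the closure trigger act on long injuries?** Assumptions: follow-up F = 365 days for the stated approximate year, onset uniform over F, no drop-out. An injury of duration d is still open at the end if its onset falls in the last d days:

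P(open) = d / F

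- 28 days: 28/365 = 0.077
- 90 days: 90/365 = 0.247
- 180 days: 180/365 = 0.493
- 270 days: 270/365 = 0.740

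For comparison, 7 days gives 7/365 = 0.019. Among closed injuries, a 180-day injury is therefore represented at (1 − 0.493)/(1 − 0.019) = 0.507/0.981 = 0.52 of the weight of a 7-day injury. Drop-out would add to the loss.

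These shares are conditional on duration. The article gives no mix of durations, so no overall percentage lost can be derived.

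**The case against.** The strongest case against the point has five parts.

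- **Other data sources exist.** The weekly e-diary asks about current injuries, amount of training and whether it is at full capacity, so an open injury leaves a weekly trace up to study end or drop-out. This stands in part: durations could be partly reconstructed. But no rule says that they will be, and the stated source of severity is the closure form.
- **Diagnosis.** A reader might infer that the diagnosis distribution is biased too, since the final diagnosis is on the same form. The article does not support that. The injury report at onset records type, symptoms, site and suspected cause. Undiagnosed absences of more than 3 weeks lead to a request for a clinical examination. The coding panel is not restricted to closed injuries.
- **The top class.** A reader might infer that absences over 6 months have no class at all. The article does not show this: the catastrophic class may be meant for them, and the reference cited for it is not at hand. What can be said is that its duration and criterion are not stated.
- **The low end.** A reader might infer that all partial time-loss injuries drop out of the severity results. That follows only if absence is the measure. If time off full training is meant, most of them get a class. The secondary split by time loss (Definitions of injury and illness) also flags non-time-loss injuries, though it does not grade them.
- **Material for a statistical analysis plan.** Handling of open incidents can be left to such a plan. It could add censoring, but the class limits, the two measures and the closure trigger are fixed here, and a later plan cannot cleanly recover closure data that were never requested.

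**Conclusion.** The point holds for the descriptive severity distribution. The rule uses two measures that disagree, leaves 0 days without a class, puts 3 months in two classes and does not define its top class. Followed as written, it gives no severity value to injuries open at study end or drop-out, and this loss rises with duration: about 8% at 28 days, 25% at 90 days and 49% at 180 days. Those shares rest on uniform onset over 365 days and on no use of the diary to fill the gap. The share of injuries with no absence is unknown until data are seen.

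A reader might infer that the main results are biased. They are not affected: the Statistical analysis plan section rests on incidence per 1000 hours and on time to injury, and neither uses injury severity. The change is worth making because it is cheap and part of the information is hard to recover later, but it does not threaten the study's primary aim.

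**What to change.** 1. Name one primary severity measure: time from the day after onset to return to full normal training. The form already asks for time off full training, and the answer can be checked against the weekly full-capacity item. Keep days fully absent as a second variable, for comparison with time-loss studies.
2. Add a 0-day class, state the duration of the top class, and make the limits exclusive, above all at 3 months.
3. Send a closure form for every incident still open at study end or withdrawal. Treat those durations as censored, and summarise duration by Kaplan-Meier, a method already planned for other data. Use the weekly diary where no form is returned.

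The cost is wording in the form and the plan, plus one form per open incident. The change should be in place before the forms go into use, and at the latest before data collection ends.

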### Sports injury research

Recent research has shown that several categories of sports-related injuries are preventable [17–19]. However, for effective implementation of injury prevention measures, comprehensive epidemiological knowledge is required [9, 20]. To reduce overtraining, injuries and illnesses, regular monitoring of athletes is an important aspect in athletic preparation [21, 22]. Although the International Paralympic Committee (IPC) has successfully implemented an epidemiological surveillance system during the Paralympic Games [23], there is still a lack of longitudinal prospective data following Paralympic athletes over entire training seasons [12]. A recent review identified large differences in injuries across sports and highlighted the need for sport-specific studies [24]. Current studies within Paralympic sport vary in quality and have mainly recorded injuries related to trauma, medical attention or time loss. Most studies are retrospective and have only recorded injuries during competitions. In addition, a diversity of injury definitions have been used and most studies have not examined impairment-related risk factors and injury severity [12, 25]. Thus, there is a need for further longitudinal epidemiological studies that prospectively assess sports-related injuries and illnesses in Paralympic sport based on risk exposure.

Today, most injury surveillance systems exist in professional and commercial able-bodied elite sport settings [26], for example soccer, tennis and rugby [27–29]. In addition, many of the surveillance systems require that medical practitioners complete the injury report form [23, 28–30]. However, the characteristics, preconditions and contexts differ between sports [31, 32]. For example, medical attention injuries may be difficult to apply when there is limited access to medical personnel [33]. It has also been proposed that some methods for injury registration may underestimate overuse injuries [34]. Also, in terms of injury capture rates, medical staff may underestimate the injury burden compared to athletes themselves [32].

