The arguments for using these definitions are based, first, on that the incidents will be recorded from the athlete’s own subjective perspective, feelings and experiences of pain, injury and illness. Second, these definitions support the concept of partial time-loss injury [33, 54]. In order to capture these injury events it is important to identify complex background patterns for overuse injuries [33, 34]. Third, this athlete population already has an existing impairment and is exposed to elements not present in abled-bodied athletes. To allow for a better understanding of sports-related injuries and illnesses in this population, we believe that it is important to assess various factors such as pain, injuries, illnesses, and psychological stressors in order to obtain a comprehensive picture of Paralympic athletes’ health. To allow comparisons with previous studies of Paralympic athletes and non-disabled athletes, the incidents will at a secondary level of the analysis be identified by time-loss and tissue damage.

In agreement with previous injury surveillance studies [28, 52] a recurrent condition will be defined as:*An incident of the same type and at the same site linked to an index incident and which occurs after an athlete’s return to full function and participation (“full recovery”) from the index recordable incident.*

The incidents will be subcategorized into re-injuries and exacerbations. Categorization of subsequent injuries – new, recurrent, exacerbation or multiple – will be taken into account using the Subsequent Injury Categorization (SIC) model before analysis [55].

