### Statistical analysis plan

The primary variables for the descriptive analyses are records of the incidence of sports-related injuries and illnesses, i.e., recordings of injury or illness events that are conditioned on that the participant is ‘healthy’ at the start of data collection period. Incidences will be calculated separately for injuries and illnesses. The incidence rates will be calculated as the number of new incidents divided by total athlete exposure hours (per 1000 h of sport participation). Health-incidents not related to sport will be analyzed separately. All events will be evaluated according to the mechanism of sports-related injuries and illnesses (independent variables). The data will be assessed for normality and will be presented using quantitative descriptive statistics (mean, median, standard deviation, minimum and maximum for continuous data and frequency and proportion (%) for categorical data). Differences in proportions between different categories (e.g., age-groups, gender, impairments, previous injury, competition frequency and level of severity of impairment) will be analyzed as covariates using chi-square statistics. The primary end point for the injury risk analyses will be time to injury. The incidence data will be further analyzed with the Kaplan-Meier survival analysis method, the log-rank test and Cox proportional hazards regression. To analyze the relationship between training loads and injury and illness incidence, Pearson product moment correlation coefficients will be used. A significance level of 0.05 and 95 % confidence intervals will be used in all tests. The data will be analyzed using IBM SPSS Statistics version 23.

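### Only an x-ray confirms a fracture or stress fracture, so cases shown on other imaging alone may be missing from that diagnostic category (minor; injury incidence unaffected)

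*Protocol article*

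**What the plan says.** The injury closure form section of the protocol article describes how diagnoses are processed. A group of two physiotherapists and two physicians "will classify each self-reported diagnosis of sports-related injuries and illnesses into a diagnostic code" of the ICD. A matrix adapted to Paralympic sport is then used to "categorize the coded injury data according to injury type (nature of injury) and anatomic location (body region"). The section ends with the rule at issue: "To confirm the diagnosis of fracture/stress fracture, an x-ray will be required". It names no other imaging and does not say how an unconfirmed case is coded.

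Two other sections decide what reaches the main results. Under the definitions of injury and illness, the injury event is "Any new musculoskeletal pain, feeling or injury that result from participation in Paralympic sport (training or competition) and cause changes in normal training/competition", whether or not time is lost. The stated reason is that "the incidents will be recorded from the athlete’s own subjective perspective, feelings and experiences of pain, injury and illness". Under the statistical analysis plan, "The incidence rates will be calculated as the number of new incidents divided by total athlete exposure hours".

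**The concern.** The rule ties a diagnostic label to one imaging method. Take two athletes with the same stress fracture, one documented on x-ray and the other only on MRI, CT or bone scan. Read literally, the rule confirms the first and not the second, although both have imaging evidence. The label then reflects the imaging that was used as well as the injury.

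At stake is the diagnostic breakdown. The fracture and stress-fracture category of the ICD coding and of the type-by-region matrix could be too low. It could also differ between groups of athletes who received different imaging, and the article plans to analyse incidents by athlete classification and impairment type. The definitions section further plans a secondary level of analysis by time loss and tissue damage, for comparison with earlier studies. A fracture without the confirmed label could be handled differently there, although the article does not say so.

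**Working it through.** The plan states no figure on this point, so there is nothing to reproduce. The check sets the sections side by side and adds one line of arithmetic.

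**1. Does an unconfirmed case leave the injury count?** No. The injury definition rests on symptoms and changed training or competition, and needs neither a diagnosis nor imaging. The incidence numerator is all new incidents, not confirmed diagnoses. Time to injury starts from the same events.

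**2. Does it lose its gradual-onset or overuse class?** No. The definitions section assigns onset by how the condition arose. The closure form section classifies by mode of onset. Neither refers to imaging.

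**3. Are mechanism data affected?** No. Onset, mechanism, anatomical site and suspected aetiology are collected on the injury report form when the injury is reported, not from the final diagnosis at closure.

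**4. Does another route confirm the diagnosis?** Not by imaging. The weekly e-diary section asks for an examination by a sports physician or physiotherapist when absence from an undiagnosed injury or illness lasts longer than 3 weeks. It names no imaging, and an athlete already diagnosed on MRI would not meet the undiagnosed condition.

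**5. What can change?** The diagnostic label, and whatever is tabulated by it.

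**6. Size.** Let K be the fractures and stress fractures documented on some imaging, and s the share of K shown only on imaging other than x-ray.

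- Confirmed under the rule as written: K × (1 − s).
- Confirmed if any imaging report counts: K.
- Proportion of K left unconfirmed by the rule: s.

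The documents give neither K nor s. The values of s below are assumptions for illustration:

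| Assumed s | Share of K confirmed under the rule | Change in total injury count | Change in gradual-onset count |
|---|---|---|---|
| 10% | 1 − 0.10 = 90% | 0 | 0 |
| 30% | 1 − 0.30 = 70% | 0 | 0 |
| 50% | 1 − 0.50 = 50% | 0 | 0 |

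Cases diagnosed only clinically, with no positive imaging, are outside K. They are unconfirmed under either rule, so none of them can be charged to the x-ray sentence.

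**The case against.** The strongest reply is that the rule does little harm and has a purpose. Diagnoses are self-reported, and one objective standard for fractures protects against false positives. The study has about 100 athletes and no stress-fracture endpoint or hypothesis, so at most one descriptive category is touched. This stands, and it is why the point is minor. It does not explain why other imaging should not count, since accepting a CT, MRI or bone-scan report keeps an objective standard.

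A reader might infer that bone overuse injuries are undercounted, and might cite the article's own statements that "some methods for injury registration may underestimate overuse injuries" and that "it is important to identify complex background patterns for overuse injuries". The documents do not support this. The first statement concerns methods of registering injuries and the second argues for capturing partial time-loss injuries. The protocol's answer to both is its broad injury definition, which the x-ray sentence leaves intact.

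A reader might also argue from the sensitivity of plain x-ray for early stress fractures, or put a large percentage on the loss. No such figure is in the documents, and the point does not need one. Counting every stress fracture not visible on x-ray as lost would also overstate the effect, because some of these would have no positive imaging of any kind.

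It is also fair to say that the article does not state what happens to unconfirmed cases. That they are moved to a pain or soft-tissue code is an inference. Nor can the closure form be faulted for lacking an imaging item: the article only summarises the form, and the form itself is not shown.

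**Conclusion.** The concern holds in a limited form. As written, the sentence makes x-ray the only evidence that confirms a fracture or stress fracture, so a case shown only on other imaging stays unconfirmed. The fracture and stress-fracture category of the ICD coding and the type-by-region matrix may be too low and may depend on the imaging used. The secondary tissue-damage analysis is possibly affected.

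The effect on injury incidence, time to injury, mode of onset and mechanism data is nil. The size of the misclassification is unknown, and the table in the check only illustrates it.

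The conclusion rests on two assumptions: that the coding group applies the sentence literally, and that at least some cases are documented only on imaging other than x-ray. Severity is minor, and the change is a cheap improvement.

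**What to change.** Replace the sentence with:

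*A fracture or stress fracture is coded as confirmed when any imaging report already obtained in the athlete's care (x-ray, CT, MRI or bone scan) shows it; if diagnosed only clinically, it is coded as suspected and shown separately.*

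Record the imaging modality and its result at closure, if the form does not already do so.

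The cost is one sentence and at most one form item. No additional imaging is requested and clinical care is not touched. The drawback is that modality and result are self-reported unless the athlete supplies the report. The change is best made before data collection starts, because the modality would be hard to recover afterwards.
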